## Study procedures

A standard operation protocol for OLGB will be used in all patients. The pouch will be made with the help of a linear stapler. At first, the stomach will be transected horizontally at the junction of the corpus and antrum at the level of crow’s foot. A small pouch is made with help of a calibration sonde of 34 French, the pouch is finished near the angle of His. Then the total limb length is measured. With a succesfull TSBL measurement the OR nurse will open the envelop and the allocated procedure will be communicated to the surgeon. Based on the randomization outcome biliopancreatic limb length is measured. In case the measurement of the total limb length does not succeed, standard limb length of 150 cm is performed. An antecolic, retrogastric anastomosis is performed by liniar stapling and the remaining defect is closed by V-loc. An anti-reflux stitch is performed. Integrity of the anastomoses is checked by methylene-blue-test and in case of leakage, extra sutures will be applied. The mesenterial defect of Peterson will be closed as far as possible by endo hernia stapling or unresolvable V-loc.

The extra measurements of limb length will take less than ten minutes of time. In patients allocated to standard treatment the surgeon will construct a BP-limb of 150 cm. In patients allocated to the adjustment length, the length of the BP-limb will depend on the total small bowel length : < 500 cm : 150 BP; 500-700 cm : 180 BP and > 700 cm : 210 BP.

On leave of the hospital the patients will be provided with Fitforme WSL Primo multivitamin capsules for the following period and will be instructed to use one capsule once daily.

Follow-up will take place in accordance with usual care, i.e. after 1,6,12 and 24 months and yearly up till 5 years. Extra visits will be at 18,30,42 and 54 months for compliance check and distribution of FFM multivitamins.

Weight measurements and blood samples will be taken in accordance with the standard protocol of follow-up after bariatric surgery in our institute added with 20 ml for selenium and copper measurements and future lab tests at 1,3 and 5 years.

Data from 6,12 and 24 months and every year thereafter up to five years after surgery will be anonymously collected in a database.

At each visit standard care includes :

- inquiry after well being and complaints, side effects, adverse events
- documenting current medication use, both regular and over-the-counter, and when applicable CPAP use
- inquiring after co-morbidities
- measurement of body weight, blood pressure and pulse
- drawing of blood samples for routine post operative care including :

CRP, hemoglobin, WBC, thrombocytes, sodium, potassium, creatinin, BUN, ASAT, ALAT, alkaline phosphatase, yGT, HbA1c, glucose, calcium, magnesium, phosphate, albumin, vit B_1_, vit B_6_, vit B_12_, folic acid, ferritin, vit A, vit D, Zinc

- Scheduling a new appointment

If the patient forgot to bring along a recent overview of current medication from their own pharmacy , the actual medication use will be requested from the local pharmacy.

Extra effort for the patient in the study includes :

- Bringing along a written overview of current medication from the local pharmacy to the appointment.
- Bringing back all used and non-used blisters and boxes for counting of compliance of the use of the FitForMe WLS primo pills
- filling in the DSS questionnaire
- filling in the RAND 36 questionnaire
- drawing of 20 ml of extra blood during the venepuncture for selenium, copper and storage for later investigations at 1,3 and 5 years
- Visits at 18, 30,42, and 54 months for counting left over pills and distributing new ones for the forthcoming 6 months

All patients will be treated with 800 IU vitamin D and 500 mg Calcium in a combination pill as part of standard care.

In case of deficiencies of vitamins or micronutrients they will be substituted according to standard care.

## Withdrawal of individual subjects

Subjects can leave the study at any time for any reason if they wish to do so without any consequences. The investigator can decide to withdraw a subject from the study for urgent medical reasons.

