## Sample size calculation

The null hypothesis in the study is as follows : the percentage TWL at five years in both groups is not different with a mean of 35. The alternative hypothesis is that the mean of the absolute difference in TWL in the experimental group is 5% more than the standard group (40% and 35% respectively).

For the evaluation of the primary endpoint of the percent total weight loss (%TWL) at five years, a sample size of 2x 92 will achieve 80% power to detect a (absolute) difference of -5.0% between the null hypothesis ( both group means of %TWL are 35.0) and the alternative hypothesis (mean of experimental group is a %TWL of 40.0) with estimated group standard deviations of 12.0 and 12.0 and with a significance level (alpha) of 0.05 using a two-sided two-sample t-test.

In case of a reduced standard deviation in the active treatment group of 9.0, the power achieved is 88.8%.

With an expected maximum drop-out due to conversion of OAGB to RYGB of 15% the sample size is 92 plus 14 = 106 patients in each group, leading to a total of 212 participants in the study.

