## Follow-up of subjects withdrawn from treatment

Patients who are withdrawn from the study remain in usual care

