## Handling of missing data

## Missing data will remain as missing, and no attempt will be made to estimate or replace missing values. Only observed values will be used in data analyses and presentations.

## Patient demographics and other baseline characteristics

## A schematic summary of the number of eligible patients enrolled and randomized will be presented by treatment strategy group. The number of subjects withdrawn from the study after randomization will be tabulated by treatment strategy group. The time and reason for withdrawal will be listed by treatment strategy group. Potential biases due to withdrawal of subjects will be investigated.

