## Secondary study parameter(s)

All secondary endpoint parameters (quantitative and qualitative) will be presented as described in section : Patient demographics other baseline characteristics.

For the evaluation of differences between groups, the primary analysis approach will be applied for the quantitative secondairy endpoint parameters..

For the qualitative parameters a Fisher exact test or a Chi-square test will be used.

For the parameters related to the occurrence of side effects, the evaluation focusses on the “absence” of differences. For these analysis estimates of risk differences with 90% confidence intervals, based on the Farrington-Manning Method will be used (non-inferiority setting, one sided approach). Due to sample size constraints, formal hypothesis tests on non-inferiority will not be performed. Multivariable logistic (or log-binomial) regression modelling is not foreseen.

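### A patient withdrawn for urgent medical reasons gives no weight, deficiency or bowel data at later visits, though usual care still measures most of it

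*Protocol*

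**What the plan says.** Section 7.4 (Withdrawal of individual subjects): "The investigator can decide to withdraw a subject from the study for urgent medical reasons". The withdrawal is from the study as a whole, and no medical reasons are listed.

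Section 7.6 (Follow-up of subjects withdrawn from treatment): "Patients who are withdrawn from the study remain in usual care". Continued entry of study data is not mentioned. Use of data up to the event is stated only for patients converted to RYGB (Specific criteria for withdrawal).

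Section 9 (Handling of missing data): "Missing data will remain as missing, and no attempt will be made to estimate or replace missing values". Only observed values are analysed. The same part of section 9 promises a listing of time and reason for withdrawal by group and an investigation of possible withdrawal bias, without naming a method.

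Section 9.2 (Secondary study parameters): "For the parameters related to the occurrence of side effects, the evaluation focusses on the" absence of differences. It uses risk differences with 90% confidence intervals and performs no formal non-inferiority test.

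Section 7.3 (Study procedures): weight and routine bloods are taken at usual-care visits to 5 years. These bloods cover ferritin, vitamins A, B1, B6, B12 and D, folic acid, calcium, phosphate, albumin and zinc. Copper and selenium are study extras at 1, 3 and 5 years.

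**The concern.** The limb length is fixed on the day of surgery, so leaving the study does not end exposure to it. What ends is the record of its consequences. On the natural reading of sections 7.4 and 7.6 with the missing-data rule, a medically withdrawn patient drops out of both numerator and denominator at every later visit, including the 5-year weight endpoint.

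Losing patients for a reason linked to the outcome is informative. If some of the urgent reasons are nutritional, the patients lost are those with the outcome being compared. Section 5 names better weight loss without more deficiencies as the potential benefit of the adjusted limb. If that limb does cause more deficiencies, removing affected patients tends to shrink the excess, which favours a finding of no difference.

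A later analysis plan cannot repair this, because it cannot analyse results that were never entered.

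**Working it through.** **The plan's own figures.** Section 4.4 says "a sample size of 2x 92 will achieve 80% power to detect a (absolute) difference of -5.0" percent, "with estimated group standard deviations of 12.0 and 12.0", "with a significance level (alpha) of 0.05 using a two-sided two-sample t-test". The normal approximation gives 2 × (1.960 + 0.842)² × 12² / 5² = 90.4, so 91 per arm. The exact t-test gives 91.4, so 92, with power 80.3%. With SD 12 and 9, the unequal-variance t-test gives 88.9%, against "the power achieved is 88.8" percent. These figures reproduce. The plan gives no figure for medical withdrawals or for the deficiency comparison; its 15% drop-out allowance is for conversion to RYGB.

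**Assumed inputs.** Control deficiency rate 20%: the Introduction cites 20% or more in the first postoperative year. Adjusted-arm rate 30%: an assumption. Evaluable patients: 92 per arm. Only affected patients are withdrawn, and none of their later results are entered.

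**Formula.** With true rate p and a share w of affected patients withdrawn before the visit, the observed rate is p(1 − w)/(1 − pw). With k affected patients removed it is (92p − k)/(92 − k).

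**Same share in both arms.** The adjusted arm has 0.30 × 92 = 27.6 affected patients and the control arm has 18.4. Removing k from the adjusted arm gives w = k/27.6, and the control arm loses 18.4w.

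| k (adjusted) | w | Adjusted | Control, same w | Difference | Difference if control loses none |
|---|---|---|---|---|---|
| 0 | 0% | 30.0% | 20.0% | 10.0 | 10.0 |
| 3 | 10.9% | 24.6/89 = 27.6% | 16.4/90 = 18.2% | 9.4 | 7.6 |
| 5 | 18.1% | 22.6/87 = 26.0% | 15.07/88.67 = 17.0% | 9.0 | 6.0 |
| 8 | 29.0% | 19.6/84 = 23.3% | 13.07/86.67 = 15.1% | 8.3 | 3.3 |

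**Wider range, same w in both arms.** For w = 10%, 25% and 50%, a true 10.0 points (20% v 30%) reads 9.5, 8.5 and 6.5. A true 5.0 points (5% v 10%) reads 4.6, 3.9 and 2.7.

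**Different shares.** With w = 10% in control and 25% in the adjusted arm, control reads 0.18/0.98 = 18.4% and adjusted 0.225/0.925 = 24.3%, a difference of 6.0. With equal true rates of 20% and the same shares, the adjusted arm reads 0.15/0.95 = 15.8%, a difference of −2.6, so it looks falsely better.

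**Same number in each arm.** Five removed from each gives 22.6/87 − 13.4/87 = 9.2/87 = 10.6 points, slightly above the truth.

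**When the difference shrinks.** With equal w, it shrinks while the rates are below (1 − √(1 − w))/w, which is 0.51 at w = 10% and 0.59 at w = 50%.

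**Scale.** With complete data on 106 per arm, the 90% half-width around 10 points is 1.645 × √(0.37/106) = 9.7 points.

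**The case against.** The case on the other side is substantial.

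- A reader might infer that the protocol removes patients for malnutrition or diarrhoea. It does not say so. Excessive weight loss, diarrhoea and nutrient deficiencies appear in section 7.7 as grounds for ending the whole trial. Section 7.3 says deficiencies are substituted under standard care, and endpoints 8 and 9 already count extra suppletion unfavourably. This stands: the link to harm is an inference.
- A reader might infer that these patients vanish from the harm comparison. They do not. The full analysis set keeps anyone with one post-baseline measurement, the safety set is all randomised patients, and serious diarrhoea, weight loss and deficiencies are reported among the serious adverse events. This stands, but those tables do not restore endpoints 8 and 9 at later visits. Withdrawal before the first database visit at 6 months can still mean complete loss.
- A reader might take the table's last column as the expected size. It removes patients from one arm only, and nothing in the protocol supports that. Investigators are blinded, so a difference between arms would mainly have to arise through the harm itself.
- Bowel-movement endpoints are quantitative and go to the t-test or Mann-Whitney approach, so the risk-difference wording does not fit them. This stands.
- Section 2 aims at fewer deficiencies and bowel movements, and for a superiority claim attenuation is conservative. That is true if the adjusted limb is better. It gives no protection if the limb is worse.
- Section 7.6 is silent on data collection rather than forbidding it. That is fair, and the silence is what needs resolving.

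**Conclusion.** The point holds as a gap in follow-up that is cheap to close. Read together, the withdrawal, follow-up and missing-data rules leave a medically withdrawn patient without weight, deficiency or bowel data at every later visit. For weight and most nutrients this loss is avoidable.

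The effect on the harm comparison is conditional. If withdrawals follow nutritional harm, the deficiency difference is probably attenuated. Under the stated assumptions this is by about 0.6 to 1.7 points out of 10 when 11% to 29% of affected patients leave both arms. It is more when the share is higher in the adjusted arm, and there is no attenuation when equal numbers leave. No withdrawal rate is given, so the real size is unknown, and in the equal-share case it is small beside the sampling error. The documents do not support saying that the harm comparison is already biased or that its worst cases disappear from the trial. The promise to investigate withdrawal bias names no method and sits beside a ban on estimating missing values.

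**What to change.** In sections 7.4 and 7.6, state that a patient withdrawn for medical reasons stops study procedures only. With the patient's consent, weight, medication and suppletion, and routine laboratory results from usual-care visits continue to be entered to 5 years and are analysed in the allocated arm. This leaves unchanged who may be withdrawn and how they are treated.

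Under Handling of missing data, add one sensitivity analysis for endpoints 8 and 9, as an exception to the observed-only rule. It applies to a patient withdrawn because of a documented deficiency who has no later result. In endpoint 8 that patient counts as not deficiency-free if the deficiency was of iron, vitamin D or B12. In endpoint 9 the patient counts as deficient only for the nutrient concerned. A blanket rule scoring every medical withdrawal as an event would be wrong: endpoint 8 is a favourable outcome, and endpoint 9 is reported per nutrient.

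The cost is protocol wording, a consent line and a little data entry. Copper, selenium, questionnaires and bowel counts may still be missing after withdrawal, because they are study extras or are not listed among usual-care measurements.

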### Specific criteria for withdrawal

Patients who are not able to swallow the FFM WSL primo capsule and those in whom the surgeon cannot measure the TSBL will be withdrawn from the study and will be replaced.

Patients who develop complications during the first 30 days needing revisional surgery changing bowel length will be withdrawn from the study.

Patients who need a conversion from the OLGB to a RYGB during the study will be withdrawn from the study and not replaced. They will be analysed on a intention to treat principle and all data up to the conversion will be used in the study.

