# STATISTICAL ANALYSIS

## Populations for analysis

## All efficacy analyses will be conducted using the full analysis set. The full analysis set will include all randomized patients with at least one post-baseline measurement and fulfilling all inclusion criteria, in accordance with the intention to treat principle (ITT).

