## The Per-Protocol analysis set is defined as those patients of the full analysis set who completed the study at 60 months and are fully compliant to all exclusion criteria. The Per-protocol analysis set will be used only if the percentage of excluded patients is substantial, i.e. > 15% of the full analysis set.

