## For qualitative parameters (categorical or ordered), frequency counts and percentages of each category will be calculated by treatment group. Percentages will be reported up to 1 decimal place.

## Primary study parameter(s)

The primary null hypothesis for this study is that there is no significant difference in the mean change in the percent of total weight loss (%TWL) at five years, between patients treated with a TSBL adjusted BP limb length (active group) versus patients treated with a standard BP limb length of 150 cm (control group).

In addition to the descriptive statistics (see the above section : Patient demographics other baseline characteristics), the two treatment strategy groups will be compared using two-sample T-test if parameter is normally distributed. Visual inspection of the distribution, as well as the Shapiro-Wilk test for normality, will used to assess normality. Unless equality of variance between groups is established, the Satterthwaite method for t-statistics and 95% confidence intervals will be used. If data is skewedly distributed, a Mann-Whitney U-test (Wilcoxon two-sample test) will be applied. For the difference in medians, the Hodges-Lehmann estimate will be used with distribution-free 95% confidence intervals.

In addition to the above mentioned analyses, the homogeneity of treatment effect over different strata of patients will be evaluated. In this, differences in treatment effect over separate strata of potentially relevant factors (e.g. gender, baseline BMI, co-morbidities, compliance, etc) will be evaluated. A multivariable model will be used to formally establish homogeneity, i.e. the absence of effect modification for the potentially relevant factors, separately.

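### Patients converted to RYGB are labelled intention to treat, but the withdrawal and missing-data rules leave them out of the primary 5-year test

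*Protocol*

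**What the plan says.** All references are to the Protocol.

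- **Specific criteria for withdrawal:** "Patients who need a conversion from the OLGB to a RYGB during the study will be withdrawn from the study and not replaced". The next sentence reads: "They will be analysed on a intention to treat principle and all data up to the conversion will be used in the study".
- **Follow-up of subjects withdrawn from treatment:** "Patients who are withdrawn from the study remain in usual care". No study measurement after withdrawal is mentioned.
- **Populations for analysis:** "The full analysis set will include all randomized patients with at least one post-baseline measurement and fulfilling all inclusion criteria", which is said to follow intention to treat. The text then assigns every patient to the allocated strategy, whatever was actually done. The per-protocol set is "those patients of the full analysis set who completed the study at 60 months" and who also comply with all exclusion criteria. It is used only if more than 15% of the full analysis set is excluded.
- **Handling of missing data:** "Missing data will remain as missing, and no attempt will be made to estimate or replace missing values", and "Only observed values will be used in data analyses and presentations". The baseline section that follows promises to list withdrawals by arm with time and reason, and to look into bias from them.
- **Primary study parameter(s):** for %TWL at five years, "the two treatment strategy groups will be compared using two-sample T-test if parameter is normally distributed", with a Mann-Whitney test if the data are skewed.
- **Sample size calculation:** 92 per arm raised to 106 for a maximum drop-out of 15%, attributed to conversion.
- **Section 8.2.3:** conversion for untreatable biliary reflux is expected in 5-10% of patients.

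**The concern.** Intention to treat on a 5-year endpoint needs the 5-year outcome of every randomised patient, or a stated way of dealing with those who lack it. Here the label is attached to a rule that stops a converted patient's data at conversion. The chosen test looks at one time point and does not use earlier weights, and the missing-data rule forbids filling the gap. Being nominally in the full analysis set does not give such a patient a value in the primary test.

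Conversion is a post-randomisation failure of the allocated operation and is followed by a different bypass. It could plausibly vary with limb length, which is the randomised factor. If it did, and if converted patients had different weight loss, the comparison of the remaining patients would no longer estimate the effect of the allocated strategies. The reader of the trial report would nevertheless be told that it was an intention-to-treat result.

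**Working it through.** **1. Following one patient through the rules.** Take a patient converted in year 3.

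- Data stop at conversion, so study weights exist for years 1 and 2 only.
- The patient has a post-baseline value and so belongs to the full analysis set.
- There is no 5-year value, none may be estimated, and both candidate tests use the 5-year value alone. The contribution to the primary test is nil.
- The earlier weights do count in the secondary %TWL analyses at 1-4 years.

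The sample size section treats conversion as drop-out, which confirms this reading.

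**2. The per-protocol set as a check.** The patients who actually enter the primary test are full-analysis-set members with a 5-year value. The per-protocol set is the 60-month completers who also comply with the exclusion criteria. On this endpoint the two nearly coincide. If conversions were the only exclusions and stayed within 15%, the threshold of more than 15% would not be passed and the per-protocol set would not be used.

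**3. The plan's sample size.** Inputs: difference 5, SD 12 in both arms, two-sided alpha 0.05.

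- The noncentral t calculation needs 91.4 per arm, so 92, with power 80.3% (stated 80%).
- With SDs of 12 and 9 at 92 per arm, power is 88.9% (stated 88.8%).
- 92 × 0.15 = 13.8, rounded to 14; 92 + 14 = 106 per arm, as stated.

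**4. Patients lost to the primary test, and power** (no other loss assumed):

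| Conversion | Lost per arm | Left per arm | Power |
| --- | --- | --- | --- |
| 5% | 106 × 0.05 = 5.3 | about 101 | 83.8% |
| 10% | 106 × 0.10 = 10.6 | about 95 | 81.5% |
| 15% | 106 × 0.15 = 15.9 | about 90 | 79.4% |
| Converters kept | 0 | 106 | 85.5% |

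At 15% in both arms the total lost is about 32 of 212. Power stays close to the planned 80% throughout.

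**5. Possible bias.** Let *c* be the share converted in an arm and *D* the mean 5-year %TWL of converters minus that of the other patients. The mean over all randomised patients is then the completers' mean + *cD*. If *D* is the same in both arms, the completers' contrast departs from the all-randomised contrast by

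shift = (difference in conversion share between arms) × *D* in size, with the sign unknown.

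The Protocol gives neither conversion shares by arm nor *D*, so every value below is an assumption:

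| Conversion by arm | D = 5 | D = 10 | D = 15 |
| --- | --- | --- | --- |
| Equal | 0 | 0 | 0 |
| 5% vs 10% | 0.25 | 0.50 | 0.75 |
| 5% vs 15% (stress case) | 0.50 | 1.00 | 1.50 |

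Against the 5-point target, 0.25-0.75 is 5-15% and 0.5-1.5 is 10-30%. Equal shares do not guarantee zero: if *D* itself differs between arms by 5-10 points, equal shares of 5-15% give shifts from 0.05 × 5 = 0.25 to 0.15 × 10 = 1.5.

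**6. Effect on the test.** With 90 per arm, SD 12 and no true difference, a shift of 0.5 gives a two-sided error rate of about 5.9%, 0.75 gives 7.0%, 1.0 gives 8.6%, and 1.5 gives about 13%, against a nominal 5%.

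**The case against.** The strongest reply is that nothing in the Protocol shows this loss to be harmful. The only reason given for conversion is biliary reflux, and no section ties it to %TWL or predicts a difference between arms. That stands. A reader might infer that the completers are an outcome-selected group; the text supports only that the loss could be informative.

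Three other inferences also go too far.

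- Setting 5% in one arm against 15% in the other joins the lowest expected rate to the maximum sizing allowance. It is a stress case and not a range the Protocol gives by arm. A *D* of 15 also exceeds the assumed SD of 12.
- The weights from years 1-4 are not thrown away. They serve a secondary endpoint and are unused only in the primary test.
- The per-protocol set is not identical to the patients observed at 5 years, because it also requires compliance with the exclusion criteria.

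It can further be said that the Protocol promises to examine bias from withdrawal, and that an SAP not at hand may say how. This is a fair point in the plan's favour, but it does not answer the concern. The test and the missing-data rule are positively stated here, and no later analysis can restore 5-year weights that the withdrawal rule keeps out of the study data.

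The loss is not a power problem either, since the sample size allows for it.

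**Conclusion.** The contradiction is established from the Protocol's own wording: intention to treat is declared, yet patients converted before year 5 have no value in the primary test. The loss is up to about 16 of 106 per arm at the 15% allowance, and about 5 to 11 at the expected 5-10%.

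Bias is possible but not demonstrated, and its direction is unknown. Under the stated assumptions it is 0.25-0.75 %TWL points for 5% vs 10% conversion and 0.5-1.5 points in the 5% vs 15% stress case. It is zero if conversion is equal between arms and non-informative. The per-protocol set offers little check on this loss. The matter should be settled while follow-up can still be arranged, because weights not kept prospectively may not be recoverable.

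**What to change.** 1. In Specific criteria for withdrawal and Follow-up of subjects withdrawn from treatment, state that conversion to RYGB does not end weight follow-up. With consent, keep recording the routine yearly weights to 5 years and include them by allocated arm in the primary analysis.
2. In Handling of missing data, add one sensitivity analysis for 5-year values that are still missing, for example a repeated-measures model on the 1-5 year weights or a delta adjustment.
3. If post-conversion weights will not be used, remove the intention-to-treat label and name the estimand that is analysed.

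**Cost.** Small changes to wording and consent. Study procedures already describes yearly usual-care visits to 5 years with body weight measured. That converted patients follow the same schedule is an inference, since the Protocol gives none for them, and should be confirmed. The 5-year value of a converted patient would then reflect the allocated strategy including the conversion, and the report should say so. Nothing in the clinical handling of conversion needs to change.
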